## 4.6 Covariates

In addition to the primary and secondary outcome measures described above, potential confounding factors will be evaluated, as follows:

- Healthy non-contacts: Age, sex, BCG status, and tuberculin/PPD reaction

- Contacts of leprosy patients: Age, sex, BCG status, type of contact, length of contact, characteristics of index case, and tuberculin/PPD reaction
- Leprosy patients: Age, sex, BCG status, type of leprosy, smear result, length of treatment, history of reaction, and tuberculin/PPD reaction
- TB patients: Age, sex, BCG status, length of treatment, and tuberculin/PPD reaction

First, the influence of these confounders on induration size and proportion positive will be evaluated at a univariate setting. Factors found to be significant at univariate level will be entered into the multivariate model. These analyses will not only be used to test the differences between groups, but will also allow us to estimate the adjusted geometric mean reaction size for each group (after transformation to the natural reaction size). The multivariate logistic regression model for “positive reaction” outcome will also allow us to obtain sensitivity and specificity, both adjusted for important confounding factors.

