### 5.1.4 Screening Subjects

Stages A and B will be performed at the following campuses in Nepal: Lalitpur Nursing Campus, Sanepa, Kathmandu; The Central Department of Microbiology, Tribhuvan University, Kirtipur, Kathmandu; and, The Institute of Medicine, Tribhuvan University, Maharajgunj, Kathmandu. Other campuses/hospitals may also be selected to participate. A total of 100 (10 for Stage A and 90 for Stage B) healthy, non-pregnant Nepali volunteers (including expatriates from India) from the above college campuses, with no known exposure to leprosy or TB, will be studied. A tuberculin/PPD test will not be performed as part of the screening process. Volunteers will be contacted directly and invited to participate after an informational talk about the research study given by the investigators at the listed campuses, one week prior to antigen administration. All subjects entering the study will be asked to read or have read to them a detailed consent form, which they will sign. Fifty individuals (5 for Stage A, and 45 for Stage B) will be randomly selected for testing MLSA-LAM and the other fifty individuals (5 for Stage A, and 45 for Stage B) will receive MLCwA. It is expected that, as with tuberculin/PPD, the two new leprosy skin test antigens will evoke negative responses in healthy, unexposed subjects.

Stage C will be performed at the following campuses in Nepal:

- AH, Kathmandu
- Lalitpur Nurses Campus, Sanepa, Kathmandu
- The Central Department of Microbiology, Tribhuvan University, Kirtipur, Kathmandu
- The Institute of Medicine, Tribhuvan University, Maharajgunj, Kathmandu

- Patan Hospital TB Clinic, Kathmandu
- Lalgadh Leprosy Hospital, Lalgadh
- Green Pastures Leprosy Hospital, Pokhara.

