patient contacts or non-exposed healthy volunteers or TB patients will inform sensitivity and specificity estimates.

The results from the 100 healthy non-contacts studied in Stages A and B will be compared to the results from leprosy patients, contacts of leprosy patients, and tuberculosis patients in Stage C. The source data document for the study will be the case report forms generated during the study.

Of those with leprosy and tuberculosis, a combination of treated and partially treated cases will be tested. Tuberculosis patients will be those who have completed the intensive phase of short-course chemotherapy and are currently receiving anti-tuberculosis medicines. The type and length of treatment completed at the time of skin testing will be recorded. The length of therapy in the case of leprosy patients may be a factor by which we categorize the skin test results in subsequent analysis.

Data collected from each leprosy and tuberculosis patient will include the extent of disease as defined by the Ridley-Jopling scale for leprosy (35), and defined as pulmonary sputum smear positive, pulmonary sputum smear negative, or non-pulmonary for tuberculosis patients (36), and the length and type of treatment. This information will be included in the CRFs. BCG vaccination is practiced in Nepal, but implementation is relatively recent and coverage by no means complete; 30% to 50% of subjects aged less than 20 have been vaccinated and the proportions will be lower for older age groups. We will record the presence and size of the BCG vaccination scar in all subjects, and this information will be used to categorize results in the subsequent analysis.

We will conduct tuberculin/PPD testing on all patients in Stages A, B, and C. We believe it is important to have a contemporaneous tuberculin/PPD test with which to compare the reactions to the leprosy skin tests to assess specificity of the leprosy skin test antigens. Tuberculin/PPD reactivity will be a measure of not only BCG vaccination, but also tuberculosis exposure, as well as exposure to non-pathogenic environmental mycobacteria, to some extent (24). Thus, in all subjects, we will be comparing diameters of the reactions to PPD with those to the new leprosy antigens.

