#### 13.6.1 Safety

Stage C-1 and C1b are intended to provide safety information on small numbers of participants (N=20 for each stage) within each of four different groups that theoretically may be at higher risk of serious adverse responses to the novel antigens. The table below shows the probability of observing 1 or more serious adverse events up to 5 or more serious adverse events, related to antigen administration. This probability is calculated from a sample of 18 subjects (20 subjects minus the possible loss of 10%) for a range of assumed "true" but unknown probabilities of a serious adverse event. Based on these results, if the true serious adverse event rate is 10% then there is an 85% chance of observing one or more serious adverse events in any one of the four groups, even if there is a 10% loss to follow-up within groups. Additional calculations, not shown, demonstrate that when there is no loss to follow-up the chance of observing at least one event increases to 88%. Aggregating the four groups and assuming 10% loss (n=72) there would still be an 89% probability of observing at least one event assuming that the groups in aggregate had a true event rate as low as 3%.

**Probability of Observing Adverse Events Within Any Study Group in Parts C-1 and C-1b Given a Range of True but Unknown Event Probabilities**

*Sample Size of 18 (assuming 2 lost to follow-up)*

| "True" Unknown Population Probability of an Event | Probability of Observing 1 or more Events | Probability of Observing 2 or more Events | Probability of Observing 3 or more Events | Probability of Observing 4 or more Events | Probability of Observing 5 or more Events |
|---------------------------------------------------|-------------------------------------------|-------------------------------------------|-------------------------------------------|-------------------------------------------|-------------------------------------------|
| -0.10%                                            | 1.78%                                     | 0.02%                                     | 0.00%                                     | 0.00%                                     | 0.00%                                     |
| 0.50%                                             | 8.63%                                     | 0.36%                                     | 0.01%                                     | 0.00%                                     | 0.00%                                     |

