### 13.6.2 Leprosy Detection/Diagnosis

The utility of a medical diagnostic test is often expressed in terms of the receiver operating characteristic (ROC) for the test (37). The ROC is a plot of the relationship between the false positive rate (FPR), or 1-specificity, and the true positive rate (TPR), or sensitivity. Given a pair of individuals, one with and one without the medical condition of interest, the area under the ROC curve (AUC) is equal to the probability that the test will correctly discriminate between this pair. This study will be the first one using these test antigens in volunteers with the condition of interest making it difficult to establish a hypothesis concerning the AUC.

The study design provides for a variety of possible subset analyses for a given dose of each antigen. Nine combinations of volunteers expected to be non-reactive and reactive respectively are listed in the following table. This is not a definitive Phase III trial, although it has some characteristics in that specificity/sensitivity are considered in the analysis, thus adjustments for multiple comparisons are not considered here. The multiple comparison possibility will be considered at the time of actual data analysis.

Although the observational unit in this study is an individual injection site, the experimental unit is subject. Since subjects in C-1 will receive the higher dose of antigen and C-1b subjects the lower dose, results from C-1 and C-1b will not be combined to construct the ROC curve or to estimate the sensitivity/specificity of the antigens. However, independently, C-1 or C-1b will be used construct the ROC curve and estimate the sensitivity and specificity for each dose of the antigen separately. The estimates and sample sizes in the remainder of this section reflect this.

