### Comparison Groups of Interest

#### ***Assuming Uniform Loss to Follow-up of 10% in each Group***

| Groups of Interest     | BT/TT Patients | Contacts of BL/LL Patients | Contacts of BL/LL Plus BT/TT Patients |
|------------------------|----------------|----------------------------|---------------------------------------|
| BL/LL Patients         | 36 and 36      | 36 and 36                  | 36 and 72                             |
| BL/LL Patients Plus TB | 72 and 36      | 72 and 36                  | 72 and 72                             |

Using a two tail-test with Type I error equal to 5% and Power equal to 80% the proposed analyses can detect a difference in area of 0.186 or less. This difference occurs for the worse case,  $AUC_0' = 0.5$  and the smallest sample size combination (BL/LL and BT/TT subjects,  $N=36$  and  $36$  respectively). Using the largest proposed sample ( $N=72$  and  $72$  for expected negative and positive responders, respectively) and a more optimistic null hypothesis of  $AUC_0' = 0.75$  results in a detectable difference of 0.101.

All of these analyses may be performed for both antigens, MLSA-LAM and MLCwA at both doses. Moreover, the ROC curves can be compared. The largest proposed sample size ( $N=72$  and  $72$  for expected negative and positive responders) is expected to be sufficient to detect a difference in the AUC in the range of 0.135 to 0.100.

This calculation is not setting a null hypothesis ( $AUC_0'$ ) for the basis of a successful study or designed to definitively test the difference in the two antigens. These values are provided however, to give an indication of the power inherent in the proposed sample size.

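### Section 4.6 chooses confounders by univariate significance, an unreliable rule for comparing non-randomized groups of this size; a short list fixed in advance would be better

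*Protocol*

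**What the plan says.** Section 4.6 (Covariates) lists age, sex, BCG status and tuberculin/PPD reaction as potential confounders in every group. It adds group-specific factors such as length of treatment, smear result and features of the index case. Each factor is examined singly against induration size and proportion positive, and then: "Factors found to be significant at univariate level will be entered into the multivariate model". No factor is forced in. The section gives no significance level for the screen and does not say whether it runs within each group or on the groups pooled. The resulting model is to test group differences and give adjusted geometric means; a logistic version is to give adjusted sensitivity and specificity.

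The groups are defined by disease or exposure. The controls are "healthy, non-pregnant Nepali volunteers (including expatriates from India) from the above college campuses" (Section 5.1.4), while the age range for all subjects is 18 to 60 years (Section 5.2). On BCG, Section 10.1 states that "30% to 50% of subjects aged less than 20 have been vaccinated and the proportions will be lower for older age groups".

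On size, Section 5.1.4 has "Fifty individuals (5 for Stage A, and 45 for Stage B) will be randomly selected for testing MLSA-LAM" and the other fifty receiving MLCwA. Stage C has 20 per group per dose, which Section 13.6.1 reduces to 18 for 10% loss. Section 13.6.2 adds that "results from C-1 and C-1b will not be combined to construct the ROC curve or to estimate the sensitivity/specificity of the antigens".

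**The concern.** A variable confounds a group comparison when it is related to both group and outcome. Whether it reaches significance alone in a small sample is a different question. A factor can miss significance because the sample is small, or because a true group effect in the opposite direction masks it, and still distort the contrast.

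Both conditions can arise here. Stage C groups are small, and recruiting controls on campuses makes a difference in age plausible, and with it a difference in BCG coverage. If the screen drops age or BCG, the result labelled as adjusted is not adjusted for it, and its interval takes no account of the selection. The screen can also pick different covariates for each antigen, dose and outcome, so the adjusted results would not be comparable with one another.

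**Working it through.** **Step 1. Group size.** The protocol gives no figure for covariate selection, so the check starts from its own calculation on the same group size. At a true event rate of 10%, P(at least one event) = 1 − 0.9^18 = 0.850 (Section 13.6.1 states 84.99%), and 1 − 0.9^20 = 0.878 (stated as 88%). So 18 to 20 is the right size for one Stage C group at one dose. The comparator is larger: 5 + 45 = 50 per antigen, or 45 after 10% loss.

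**Step 2. Power of the screen.** The level is assumed to be 5% two-sided, the only test level the protocol gives (for the AUC calculation in Section 13.6.2). For a factor with correlation r with induration, power ≈ Φ(√(n−3)·atanh(r) − 1.96), the other tail being negligible or nearly so. For r = 0.3, atanh(r) = 0.3095.
- n = 18: √15 × 0.3095 = 1.199, and Φ(1.199 − 1.96) = 0.22.
- n = 50: √47 × 0.3095 = 2.122, and Φ(2.122 − 1.96) = 0.56.

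| r | n = 18 | n = 50 |
|---|---|---|
| 0.2 | 12% | 28% |
| 0.3 | 22% | 56% |
| 0.4 | 37% | 83% |

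A binary factor does no better: split 9 v 9 in a group of 18, with 50% v 75% positive reactions, it is retained 19% of the time.

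**Step 3. Bias left in the contrast.** The protocol gives no confounder strength, age gap, age spread or induration SD, so everything in this step is assumed. The model is y = group effect + slope × age + N(0,1), with 50 controls, 18 patients and a mean age gap of 1 patient SD. The slope is 0.2 to 0.4 residual SD per patient SD of age. The control age SD is either equal to the patients' or half of it, and the group effect is 0, or 0.5 SD in the same or the opposite direction. Without adjustment the bias is slope × gap, that is 0.2 to 0.4 SD. Under the plan's rule the age-adjusted contrast is used if the screen gives p < 0.05, and the unadjusted contrast otherwise.

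| Screen | Group effect | Share of bias left |
|---|---|---|
| Within patients | any | about 53–83% |
| Pooled | none | about 3–50% |
| Pooled | same direction as bias | close to none, up to 15% |
| Pooled | opposing | about 15–90% |

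The nominal 95% interval misses the true difference (the type I error when that difference is zero) in about 9% to 22% of runs with the within-patient screen and about 4% to 13% with the pooled screen. With age always in the model, the bias is about zero and the error about 5%. That last result follows from fitting the same model that generated the data, so it does not show that adjustment removes all confounding in practice.

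**Step 4. A setting kinder to the plan.** Pool all five groups (45 + 4 × 18 = 117), with a slope of 0.3 or more and gaps of 0.5 or 0.8 SD. The confounder is then kept in 90% to 100% of runs, with about 0% to 7% of the bias left, when the group effect is absent or in the same direction. With an opposing effect it is kept in 68% to 99%, with 1% to 23% left. At a slope of 0.2 with an opposing effect it is kept in 26% to 33%, with 53% to 60% left.

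**The case against.** The model is meant to compare groups, so a pooled screen is a natural reading of Section 4.6. On that reading a moderate continuous confounder is usually kept and the type I error stays near 5% when there is no group effect. The comparator is also not 18 to 20 but about 50 per antigen. A reader might infer that the screen will usually discard real confounders and leave most of their bias. The document does not support that as a general statement: it is so for a screen within one small group, for weak factors, or when the group effect opposes the bias. Even the upper part of the pooled range with no group effect requires a narrower age spread in controls than in patients, which is plausible on a campus but not stated.

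A reader might also infer that age and BCG differ between groups by design. The 18 to 60 range applies to everyone; an age gap is likely, but its size is unknown.

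Section 10.1 gives these factors another role: subjects are to be stratified by age and gender, and BCG scar data are to be used to categorize results. That is a real provision, but it does not alter the model in Section 4.6. Section 13.5 says that no formal hypothesis is tested. That lowers the weight of the type I error figures but not of the bias, since estimates are biased just as tests are, and Section 4.6 promises both.

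Finally, forcing covariates in has its own risks. Healthy subjects are expected to react negatively, so the logistic model may have few events; and if ages barely overlap, linear adjustment extrapolates. Both are reasons to keep the list short, not to let a p-value choose it.

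**Conclusion.** The point stands as a criticism of a rule the protocol fixes, not of a detail left open. Univariate significance is an unreliable way to choose confounders when campus controls are compared with Stage C groups of 18 to 20 per dose. The firmest figures are the retention probabilities in Step 2, which need only the assumed 5% level and a correlation. The bias figures are conditional: from almost none to about 90% remains, according to how the screen is pooled, how strong the confounder is, how far apart and how spread the ages are, and which way the group effect runs. None of these is given, and the answer turns on pooling, which the section leaves unstated.

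The reach is limited to the adjusted group comparisons and the adjusted sensitivity and specificity of Section 4.6. A reader might extend the criticism to the cut-offs and ROC curves, but Section 13.9.3 bases those on induration and does not mention the covariate model. The change is worth making because it is cheap; the study's main diagnostic estimates do not depend on it.

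**What to change.** In Section 4.6, replace the univariate screen for between-group models with a short list fixed in advance (age, sex and BCG scar), kept whatever the p-values and the same for each antigen, dose and outcome. Keep group-specific factors, such as length of treatment and index-case features, for description within groups. State whether PPD reaction is adjusted for or analysed separately.

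The cost is wording only, since all three variables are already collected. The statistical cost is up to three degrees of freedom and slightly wider intervals. If positive reactions are few, the logistic model may need a penalized (Firth) fit. If the ages of controls and patients barely overlap, report the adjusted contrast with that limitation.

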## 4.7 Interim Analysis Plans

Upon the completion of each stage, The EMMES Corporation will analyze and compile data into a safety report to be reviewed by the SMC. Data from Stage A will be reported “blinded,” since Stage A is merely a ramping stage for Stage B. Following Stage B, both Stage A and B will be unblinded and analyzed together. Upon review of Stages A/B, C-1 and C-1b, the SMC will compose a report to be sent to DMID, NHRC, and CSU IRB. In all cases of unblinding, the identity of antigens will only be made available to key study personnel.

## 4.8 Safety Oversight, per DMID Guidelines; SMC

An on-site, qualified physician will serve as an Independent Safety Monitor (ISM). This individual will be responsible for reviewing all adverse events (AEs) and serious adverse events (SAEs) and reporting the findings to the Principal Investigator or Subinvestigator, who will forward the report to PPD Development Inc., DMID's pharmacovigilance contractor, and DMID. The ISM will also serve as a member of the SMC. The SMC consists of 4 physicians with extensive experience in leprosy and/or tuberculosis disease, and 1 biostatistician. The purpose of this committee is to review all serious adverse events that occur in the study, based on information that will be provided. They will then analyze all serious adverse events (SAEs), and make recommendations to DMID, NHRC, and CSU IRB, as to whether the study should be stopped or the protocol altered, as necessary. Reasons to stop the study will include, but not necessarily be limited to, any severe anaphylactic reaction to one or both of the new skin test antigens. Severe ulceration and necrosis at the skin test antigen sites or

urticaria, or an anaphylactic reaction would also be reasons for stopping the study temporarily for review and advice before potentially proceeding.

## 5 STUDY POPULATION

### 5.1 Selection of the Study Population

Three campuses have been identified to perform Stage A and B: Lalitpur Nursing Campus, Sanepa, Kathmandu; The Central Department of Microbiology, Tribhuvan University, Kirtipur, Kathmandu; and, The Institute of Medicine, Tribhuvan University, Maharajgunj, Kathmandu. Four additional campuses have been identified to perform Stage C: Patan Hospital TB Clinic; Lalgadh Leprosy Hospital; Green Pastures Leprosy Hospital; and AH. Other campuses/hospitals may also be selected to participate. All participants will be residents of Nepal, including expatriates from India, because they have been exposed to similar environments, as opposed to expatriates from other countries. Of these 260 individuals, 100 will be healthy non-contacts, 40 will be cases of leprosy from Lalgadh Leprosy Hospital, Green Pastures Leprosy Hospital, and AH, 40 will be healthy contacts of BL/LL and/or BT/TT leprosy patients, and 40 will be tuberculosis patients recruited from the Patan Hospital TB clinics. A leprosy contact is defined as a co-inhabitant of a leprosy patient for a duration of at least six months, and within 6 months of enrollment into the study or a person who has been professionally exposed to leprosy for a duration of at least 5 years and within 6 months prior to enrollment in the study. Enrollment of contacts of leprosy patients for Stage C-1 and Stage C-1b will include only co-inhabitants of BL/LL leprosy patients. The duration of contact with the index case, and details of the index case will be recorded in the CRFs. The volunteers will be free of intercurrent tuberculosis, and will not have been taking immunosuppressive therapy for at least 4 weeks prior to study enrollment.

